#### Other outcomes measures

Advantages and disadvantages of the Hospital at Home care programme will be assessed through multiple instruments and questionnaires. The instruments are validated and used in community-dwelling older patients with cognitive disorders. Additional data will be collected on the time spent at home (home time); total number of days alive and out of the hospital or a skilled nursing facility in the 6 months following the randomisation at the ED,^31^ the number of transfers (home↔hospital) and the number of healthcare professionals involved.

Cost data will be collected, as described by Drummond *et al*, including the costs to the healthcare system, patients and families, and other sectors.^32^ The volume of care use will be extracted from hospital files and combined with the reference cost values, as provided by the cost guidance module of the Dutch National Health Care Institute.^33^

### Process evaluation

A process evaluation will be conducted as part of the feasibility study to understand the barriers and facilitators to participate and to gain an understanding of the experiences and perceptions of Hospital at Home care of participants and healthcare professionals. From all eligible patients who declined to participate, data concerning the patient characteristics and reasons for non-participation will be collected. At the end of the trial, a representative sample of participants and/or their informal caregivers will be invited for an interview to evaluate their experiences receiving Hospital at Home care. The interviewer will not be a an active member of the research team or involved in day-to-day care and will explore independently how the participants perceived Hospital at Home care, including the contact with the health professionals and the impact of Hospital at Home care on their lives and their caregivers’ personal lives. In case of participant dropout, efforts will be made to obtain an understanding of why the participants did not complete the trial.

In addition, a representative sample of healthcare professionals, consisting of physicians and nurses working in the ED, physicians and nurses providing the Hospital at Home care, and general practitioners, will be asked to participate in a face-to-face interview. The healthcare professionals will be asked about their experiences and opinions about the H@H trial and Hospital at Home care. All interviews will be transcribed verbatim, and a framework analysis will be used as the method of qualitative data analysis.^34^

### Data management

All data will be entered in an electronic trial-specific database, with the participants identified by a unique trial number. Confidentiality of participant information will be maintained throughout the trial. Information can only be traced to the participants by designated researchers. The database will be stored and maintained by Castor Electronic Data Capture, compliant with GCP guidelines and the European Data Protection Directive (Castor Electronic Data Capture, 2017; Ciwit BV, Amsterdam, the Netherlands). Data will be stored for a maximum period of 15 years after the study has ended, according to Dutch law.^35^

### Statistical analysis

The participant flow diagram, according to Consolidated Standards of Reporting Trials (CONSORT) guidelines,^36^ will provide a summary of the recruitment and declination rates in percentage (%) at baseline, discharge and 3-month and 6-month follow-ups. Distributions of the data at baseline, discharge and 3 and 6 months after randomisation will be explored, with unusual values noted and explained. Variables will be summarised as the n (%), mean (SD) or median (IQR) for each group to characterise the sample and search for any imbalances. The percentages, means and SD, and medians and IQRs will be calculated to describe the quality of care and the advantages and disadvantages of Hospital at Home care at baseline, discharge and 3-month and 6-month follow-ups.

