## Methods and analysis

### Trial design

The design is a randomised controlled feasibility trial and will use a process evaluation. This study will be conducted at the medical emergency department (ED) of the academic hospital of the University Medical Center of Groningen in the Netherlands and will evaluate cognitively impaired older patients who are in need of acute hospital care. Figure 1 shows the trial design summary. Participants will be randomised to either Hospital at Home care or usual hospital care in a 4:1 ratio, respectively. Patients will be randomised using a computerised random number generator (http://www.randomization.com), including block randomisation.

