### Sample size of study population

Based on the numbers available from the ED of the University Medical Center Groningen, the Netherlands, we calculated that an average of 3990 older patients 65 years and over is admitted to our medical ED each year. The Hospital at Home trial will be introduced during working hours, which provides an estimated 1900 patients per year. Not all 1900 patients will be eligible for study inclusion. Based on screening of ED medical records, approximately 15% of the patients meet the eligibility criteria for Hospital at Home care, resulting in 285 eligible persons per year. In recent randomised controlled trials (RCTs) of Hospital at Home care in Italy, 54% and 57% of the eligible patients was willing to participate and gave informed consent.^28 29^ We presume a similar consent rate of 50%, as described in these previous clinical trials, and expect for 143 patients to be included.

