### Timing of measurements and outcome measures

Data will be collected at baseline at the ED, during admission (in Hospital at Home or hospital), at discharge and at 3 and 6 months following randomisation, plus or minus 2 weeks. An overview of the timing of measurements and outcome measures are shown in table 2.

**Table 2 T2:** Overview of the content and description of outcome measures and timing of measurements

	Description and instrument	Timing of measurements					
		Screening	Baseline	Admission	Discharge	3 months	6 months
Degree of illness based on physiological parameters	Vital signs alarm score; Modified Early Warning Score^48^	R					
Cognitive impairment	4AT test for delirium*, six-item cognitive impairment test for cognitive impairment*^42 49^	R					
Sociodemographics	Date of birth, nationality, household composition, marital status, highest level of education		R				
Health status	Charlson Comorbidity Index*^50^		R				
Identifying at-risk patients	Safety management system patient screening (VMS)^51^		R				
Functional status	Activities of daily living (ADL), modified Katz-ADL index score^52^		R		R	R	R
Health status	EuroQol-5D-5L*^53^		R		R	R	R
(Health-related) quality of life, well-being	Icepop capability measure for Older people (ICECAP-O)*^54^		R		R	R	R
Caregiver burden	Self-rated burden scale*, caregiver strain index*^55 56^		C		C	C	C
Medical consumption	Imta Medical Consumption Questionnaire (imcq)*^57^		P,C			P,C	P,C
Hospitalisation-associated geriatric syndromes	Infections, falls, pressure injuries, in case of delirium; delirium observation scale score (DOSS)^58^ and use of physical or chemical restraints, total days with a urinary catheter			N			
Nutrition	Malnutrition Universal Screening Tool (MUST)^59^		N				
	Food intake, fluid intake			N			
Pain	Numeric Rating Scale-score (NRS) for pain^60^			N			
Health perception	(Rotterdam) symptom checklist*^61^			N			
Immobility	Hierarchical assessment of balance and mobility (HABAM)^62^			Ph			
Satisfaction with care	Client Satisfaction Questionnaire 8 (CSQ-8)*, care evaluation question*^63 64^				P P, C, N, D		
Mortality	Mortality at 30 days, 3 months and 6 months after baseline*				N	R	R
(Re)admission hospital	Length of stay, readmission rate at 30 days, 3 months and 6 months after baseline*				N	R	R

Assessed by: C, caregiver; D, doctor; N, nurse; P, participant; Ph, physiotherapist; R, research nurse.

*All assessments are extra for trial purposes and are not part of the medical treatment.

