#### Feasibility

For the participation rates, the proportion of participants per step will be calculated. The reasons for non-participation and data concerning the characteristics of non-participants will be collected. We consider the participation rate feasible when it is similar to the participation rate as is described in previous RCTs and around 50% of the eligible patients will consent to participate.^28 29^ Quality of care will be measured by collecting data on patient, institutionalisation (eg, to the hospital or nursing home), mortality, activities of daily living functioning, prevalence of hospitalisation-associated geriatric syndromes, the length of stay in the hospital or Hospital at Home care programme and contact with healthcare professionals. The study is considered feasible if the quality of care of Hospital at Home care on these measurements is non-inferior to usual hospital care.

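### Feasibility depends on ADL being non-inferior to usual care, but the stated analysis gives only raw summaries by arm, with about 29 controls and no use of the baseline Katz-ADL score

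*Protocol article*

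**What the plan says.** The protocol article sets a between-arm criterion. In the Feasibility section the study "is considered feasible if the quality of care of Hospital at Home care on these measurements is non-inferior to usual hospital care". The measurements listed just before that sentence include ADL functioning, together with institutionalisation, mortality, geriatric syndromes, length of stay and contact with professionals. No margin is given.

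The Statistical analysis section is descriptive. "Variables will be summarised as the n (%), mean (SD) or median (IQR) for each group"; that sentence goes on to give the purpose as characterising the sample and looking for imbalances. The next sentence covers outcomes: percentages, means with SD and medians with IQR, to describe quality of care and the advantages and disadvantages at baseline, discharge, 3 and 6 months. Nothing is said about what follows if an imbalance is found.

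Table 2 lists "Activities of daily living (ADL), modified Katz-ADL index score" at baseline, discharge, 3 and 6 months. EQ-5D-5L, ICECAP-O and the caregiver burden and strain scales follow the same schedule but are not on the Feasibility list.

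The strengths and limitations box says that, because of the limited sample size, the results will not show effectiveness against usual care.

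**The concern.** The Feasibility criterion needs an estimated difference between arms and a statement of its uncertainty. The stated analysis produces neither. It produces two columns of summaries, and someone must then decide by eye whether ADL under Hospital at Home care is no worse.

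The 4:1 allocation makes that reading fragile, because the usual-care mean rests on few patients. If the arms differ in ADL at entry by chance, part of that difference carries into the follow-up means and can look like benefit or harm. Looking for imbalance does not remove it, and without a planned response its handling would be chosen after the data are seen. The baseline score that would deal with this is already being collected.

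**Working it through.** **Inputs from the protocol article**
- Patients in working hours: "which provides an estimated 1900 patients per year" (Sample size of study population).
- Eligibility: "approximately 15% of the patients meet the eligibility criteria for Hospital at Home care, resulting in 285 eligible persons per year" (same section).
- Consent: "We presume a similar consent rate of 50" per cent (same section).
- Total: "expect for 143 patients to be included" (same section).
- Allocation: "Participants will be randomised to either Hospital at Home care or usual hospital care in a 4:1 ratio, respectively" (Trial design).

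**Reproducing the plan's figure**
- 1900 × 0.15 = 285 eligible per year.
- 285 × 0.50 = 142.5, rounded to 143. The figure reproduces. It is a recruitment projection, not a power calculation.
- At 4:1, controls = 143 / 5 = 28.6, about 29. The intervention arm is about 114.

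**Precision of a raw difference in means (SD units, normal approximation)**
- SE = √(1/114 + 1/29) = 0.208.
- 95% half-width = 1.96 × 0.208 = 0.41 SD.
- If the observed difference were exactly zero, the interval would still reach 0.41 SD against Hospital at Home care. That result could not meet any margin narrower than 0.41 SD.

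**Chance imbalance at baseline on any one scale**
- P(difference above 0.25 SD either way) = 2 × [1 − Φ(0.25 / 0.208)] = 0.23.
- For the same 143 split 1:1, SE = √(2/71.5) = 0.167 and the probability is 0.13.
- P(difference above 0.5 SD) at 4:1 = 0.016.

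**Effect of adjusting for baseline**

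The article gives no baseline to follow-up correlation r, so r is assumed over a range. The adjusted half-width is 0.408 × √(1 − r²). A baseline imbalance of 0.25 SD carries r × 0.25 into the raw follow-up difference.

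| Assumed r | Unadjusted half-width | Adjusted half-width | Carried over from a 0.25 SD imbalance |
|---|---|---|---|
| 0.3 | 0.41 SD | 0.39 SD | 0.075 SD |
| 0.5 | 0.41 SD | 0.35 SD | 0.125 SD |
| 0.7 | 0.41 SD | 0.29 SD | 0.175 SD |

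**Losses**

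These figures use all 143 patients. No dropout rate is stated. With equal losses in both arms, the unadjusted half-width 1.96 × √(1/[114(1 − d)] + 1/[29(1 − d)]) becomes 0.43, 0.46 and 0.49 SD for assumed losses d of 10%, 20% and 30%.

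**The case against.** The strongest reply is that this is a feasibility trial that disclaims effectiveness, that description suits such a trial, and that covariate adjustment is ordinarily left to an analysis plan or full protocol, neither of which is shown. The article does not rule adjustment out, and it does plan to look for imbalance.

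Much of this stands. The mere absence of an adjustment model from a journal article is not an error. For EQ-5D-5L, ICECAP-O and caregiver strain no decision rule is stated, so plain summaries are defensible. What does not fall away is ADL: the article itself makes the feasibility verdict depend on a between-arm comparison that includes it, then describes an analysis that cannot deliver that comparison. The disclaimer about effectiveness does not cancel the criterion.

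The size of the harm should also be kept in proportion. Imbalance above 0.25 SD on a given scale is possible (23%), not probable. Baseline values are to be reported, so a marked difference would be visible. Baseline is taken in the emergency department during acute illness, so a low correlation is plausible; at 0.3 the gain in precision is small.

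Finally, adjustment alone does not repair the criterion. An adjusted difference without a margin still cannot show non-inferiority.

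**Conclusion.** The point holds for ADL. The Feasibility criterion and the Statistical analysis section do not fit together, and following both as written gives a comparative verdict from side-by-side raw summaries. With about 114 and 29 patients, a mean difference is known only to about ±0.41 SD, with a 23% chance of a baseline difference above 0.25 SD on any one scale. Adjusting for baseline Katz-ADL would bring the half-width to between 0.39 and 0.29 SD for correlations of 0.3 to 0.7. Those correlations are assumed, and no dropout or death is allowed for.

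A reader might infer that the unadjusted comparison is biased. It is not: randomisation keeps it unbiased on average, and the gain from adjustment is precision and protection from the chance imbalance of the one trial that is run. A reader might also infer that all four repeated scales are equally affected. Only ADL is on the list that feeds the criterion.

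The change is worth making, since it costs almost nothing, but it does not put the trial's recruitment and acceptability aims in doubt.

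**What to change.** 1. In the analysis section, add for Katz-ADL the between-arm difference at discharge, 3 and 6 months from a linear model adjusted for the baseline Katz-ADL score, with a 95% CI. Label it as estimation among survivors and report deaths by arm beside it, because a follow-up ADL score exists only for those alive.
2. Base the ADL part of the Feasibility judgement on that estimate and not on raw group means.
3. Make the criterion agree with the disclaimer about effectiveness and with the analysis section: either state a margin against which the interval will be read, or replace the non-inferiority wording with wording about estimating the difference and its uncertainty.
4. Optionally, report the same baseline-adjusted estimate for EQ-5D-5L, ICECAP-O and caregiver strain, as description only.

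The cost is a few lines of text and one model per time point. No new data are needed, since the baseline score is already in Table 2. Choosing a margin, if that route is taken, needs a justification that the article does not now contain.

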### Monitoring and participant safety

Although, the H@H trial is considered to be a low risk trial, the participant safety will be monitored by an independent Data Monitoring Committee (DMC). The DMC will consist of two members: an experienced clinician and an epidemiologist. Members of the DMC are independent of the trial and will discuss each individual participant with serious adverse events. The DMC will receive and review the serious adverse events and evaluate the risk involved with negative outcomes. The DMC is authorised to make recommendations to temporary put on hold or ending the study prematurely when participant safety is an issue, based on their findings. All serious adverse events will be reported to the principal investigator within 24 hours of knowledge of the event and then subsequently reported to the Dutch portal for medical research involving human subjects.

## Discussion

Reducing unwanted hospital admissions in older patients with cognitive impairments and facilitating patient-centred care in a patient’s preferred location is a goal worthy of pursuing. This goal aligns with the tenet of the current Dutch government and the advice provided by the Dutch Council for the Environment and Infrastructure: to actively promote and enable people to live independently in their own homes for as long as they desire.^37^ Previous trials and a recent review have confirmed that alternative management strategies for low-risk patients with acute medical conditions conventionally treated through hospitalisation exist with positive impact on patient satisfaction, are effective and can be safely achieved in lower cost settings.^22 23 38^

Introducing a Hospital at Home care trajectory in the Netherlands is incited by the principles of value-based healthcare: improving the patients experience of care and as a result of this process reducing the costs.^39^ All countries with an ageing population experience pressure, in terms of shortage of (emergency) hospital beds and rising healthcare costs. Hospital at Home care could be shown beneficial in facilitating higher valued care for patients and their caregivers without additional costs. Benefit should be measured in other outcomes than clinical indicators such as mortality. To illustrate, one of the outcomes of a future RCT could be the time spent at home. Time spent at home has been defined as the total number of days alive and out of the hospital or a skilled nursing facility in the 6 months after hospital admission.^31^ It has been used as a primary outcome in a follow-up study of older patients with acute hospital admissions, and has been demonstrated to be of more importance in older patients.^17 40 41^ Evaluation of time spent a home in this feasibility study could support estimating a sample size based on a patient-relevant outcome in a future RCT.

This study will be the first to investigate the feasibility of providing acute hospital care at home for older patients with cognitive impairment in the Netherlands. Studying Hospital at Home care and identifying the barriers and facilitators will support the implementation of Hospital at Home care and break new ground for a future RCT investigating the (cost-)effectiveness.

## Ethics and dissemination

The trial will be conducted in accordance with the Declaration of Helsinki 1996, principles of good clinical practice and the University Medical Center of Groningen Research Code. Any protocol amendments will be submitted to the ethics committee. A register of the protocol amendments will be available in the study protocol.

The results of the trial will be reported according to the CONSORT guidelines and will contribute to knowledge of the implementation of Hospital at Home care and patient-centred acute care for older patients with cognitive impairment. The study will also contribute to the knowledge of the transmural cooperation and costs of providing care, in terms of the translocation of hospital care to home. Regularly updates will be published on the study website and in newsletters. Conferences and meetings will be held for all involved healthcare professionals. Participants who requested information on the study will be sent a lay summary. A publication policy will be agreed on with co-applicants. The study findings will be published in relevant peer-reviewed journals.
